**Methods:**

We will conduct a prospective longitudinal cohort study of 600 beginner meditators in Australia, New Zealand, the United States, and the United Kingdom over a 1-year period. Meditation practice frequency and duration will be reported weekly through the ambulatory assessment app Fabla (Emory University), with sampling of the primary outcome of quality of life and secondary outcome of mental well-being at monthly intervals. Practice characteristics, including secular versus spiritual practice, will also be reported monthly, as will the costs of meditation and mental health care and the incidence, severity, and duration of any adverse effects. Potential confounders, including baseline mental health symptoms, social support, and sociodemographics, will be controlled for in linear mixed models. An incremental cost-effectiveness ratio will be calculated, and sensitivity analyses will be conducted.

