### Participant Selection Criteria

We will recruit beginner meditators who have completed initial instruction in MBPs and 2 Buddhist traditions that have informed MBPs, Theravada, and Mahayana [50]. While all these traditions emphasize a focus on observing experiences and one’s responses to experiences, spiritual traditions often interpret these processes via specific lenses (eg, the Four Noble Truths in Theravada) and soteriologies that affect implicit and explicit motivations for a practice [51]. In addition, each tradition has exclusive introspective and reflective tools (eg, koans in Zen within Mahayana) that may be applied within meditation practices or in other aspects of life. Furthermore, the practice, social, and community contexts vary widely (eg, spaces, teachers, rituals, and other activities). The inclusion of these traditions will facilitate rich insights into the effects of diverse settings while keeping a meaningful focus.

Participants will be included if they are adults aged 18 years or older; reside in Australia, New Zealand, the United Kingdom, or the United States; have completed an initial introductory meditation course, initial instruction, or regular practice (at least 40 minutes per week) for at least a month in one of the eligible traditions (Buddhist Mahayana or Theravada or mindfulness meditation, including MBPs and apps that incorporate mindfulness meditation) in the last 4 months; and if they intend to continue practicing meditation regularly in the eligible meditation tradition. We are recruiting participants with some meditation experience rather than those with no lifetime practice hours to examine a naturalistic sample of people who independently seek out and continue meditation practice. This sample will also support the study retaining participants who continue practicing meditation for one year, and therefore have sufficient power in our primary analysis, as significant dropout is common in the first weeks of meditation practice [52-55].

Participants will be excluded if they have less than one month of experience in their meditation practice (with the option to defer enrollment until they satisfy this criteria), if they have regular meditation experience (meditating at least 40 minutes per week) for one month or more in any tradition prior to the last 4 months, or if they are monastics or have a similar formal role in a religious community and/or they reside in a religiously affiliated dwelling (eg, monastery).

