For hypothesis 1, we will perform linear mixed model analysis of the fixed effect of the amount of meditation in the past month on quality of life in the past week (EQ-HWB-9), controlling for the potentially confounding baseline factors of age, caring status, education, mental health diagnosis, commitment to meditation practice, and membership of a meditation practice community at baseline. This model will allow us to assess how meditation as practiced by our participants under naturalistic conditions contributes to their quality of life, controlling for baseline differences related to time available for practice, symptom severity, motivation, and social support. If we detect an effect of meditation practice, we will perform sensitivity analysis to examine how robust this effect is to time-varying confounders by using inverse probability weighting of meditation in the last month to examine if the association would still be present if practice that month had varied independently of prior practice and benefit.

For hypothesis 2, we will perform linear mixed model analysis of the fixed effect of the amount of meditation in the past month on mental well-being in the past 2 weeks (SWEMWBS), controlling for the potentially confounding factors of age, caring status, education, mental health diagnosis, commitment to meditation practice, and active membership of a meditation practice community at baseline. If we detect an effect of meditation practice, we will again perform time-varying confounding sensitivity analysis with inverse probability weighting.

For hypothesis 3, we will add the variable capturing whether participants practiced secular meditation traditions (with no more than one month of reported practice in a spiritual tradition) versus engaging in spiritual traditions and its interaction term with the amount of meditation to the model for hypothesis 1. This initial analysis will allow us to assess whether predominantly secular meditation has a differential effect from meditation that incorporates spiritual practices, as practiced in real-life contexts, while retaining sufficient power. If we detect an effect, we will perform further exploratory analysis into what may be driving this difference. We will also describe the groups in terms of meditation practice characteristics, including proportion of practice types and social context.

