For hypothesis 4, we will add the secular versus spiritual variable and its interaction term with the amount of meditation to the model for hypothesis 2.

To address aim 5, we will conduct an exploratory cost-effectiveness analysis using participants who did not continue meditating as a comparator to participants with ongoing meditation practice, while accounting for relevant confounding factors. We will use the EQ-HWB-9 to measure outcomes, applying index values from the United Kingdom pilot value set over time to create QALYs [60]. Costs will include those for mental health service use (psychological support) across one year plus costs of meditation practice. To calculate the incremental cost-effectiveness ratio (ICER) from a public health perspective, we will calculate the difference in costs between the low- and high-meditation dosage groups and divide by differences in QALYs. The ICER represents the additional cost of the intervention for each additional unit of health benefit gained. We will investigate the cost-effectiveness of the ICER against thresholds of the 4 included countries, as available, to determine how likely the intervention will be cost-effective from a public health perspective. Issues of confounding will be addressed through statistical adjustments as per the main analysis, and we will conduct relevant scenario analyses. We will conduct deterministic (one-way) sensitivity analysis to estimate the impact of uncertainty around effects by varying output and cost parameters, displayed on tornado graphs. We will conduct probabilistic sensitivity analysis to explore the combined parameter uncertainty over 10,000 iterations, displayed on a cost-effectiveness plane.

To address aim 6, we will estimate the incidence of participants first reporting adverse effects by reporting the proportion and confidence intervals of first adverse experiences that also impaired participants’ daily function. We will also report descriptive statistics of the frequency, severity of impairment of daily function, and duration of impairment of meditation-related challenging experiences and MRAEs.

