The study also aims to conduct an economic evaluation in the form of an exploratory cost-effectiveness analysis to investigate costs and outcome comparisons associated with regular meditation practice. As this study is a cohort study and not an RCT where we would usually see cost-effectiveness analysis conducted, and as there is no control group, we plan to construct an exploratory cost-effectiveness analysis using a comparator group of those not continuing to meditate. This is a major limitation to the cost-effectiveness analysis proposed in this study.

There are further limitations regarding effects and costs. Although the EQ-HWB-9 has been shown to be valid for measuring quality of life in people who meditate [76], there are currently no country-specific value sets for the EQ-HWB-9 for Australia, New Zealand, or the United States. We will have detailed information on costs due to psychological care; however, we will need to estimate costs from this information for the relevant country’s health systems where costs are not out-of-pocket. This analysis is further exploratory on the basis of the direction of the effect. For instance, if, through partaking in meditation practice, participants decide to pursue mental health support, this will increase costs but may also increase outcomes. Hence, lowering mental health support costs may not be the objective here. We acknowledge the potential opportunity cost of meditation practice, and while we will be able to provide information on the time commitment needed to achieve benefit in our primary analysis, we are unable to address this in the current exploratory cost-effectiveness analysis. As the outcomes look at change in QALYs over one year, we will also not be able to take into account changes in effects and costs during this period for the base analysis. We may be able to do further exploratory analysis investigating the associations between costs and effects over time in a future study.

Finally, the study aims to estimate the incidence of MRAEs. We anticipate the incidence of MRAEs will be around 10%, in line with previous research [42]. We also expect the average impact on daily function to be small, on average, but that some participants will experience significant impairment to daily function. We plan to conduct a future mixed methods examination of MRAEs to explore their predictors and phenomenology.

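### Country of residence is in none of the adjustment sets, which matters most for the Aim 5 cost comparison, where unit costs depend on country

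*Protocol article*

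**What the plan says.** The abstract plans "600 beginner meditators in Australia, New Zealand, the United States, and the United Kingdom", and the selection criteria require that participants "reside in Australia, New Zealand, the United Kingdom, or the United States". Country is therefore known for everyone from screening.

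In the Analysis Plan, the hypothesis 1 model adjusts for "potentially confounding baseline factors of age, caring status, education, mental health diagnosis, commitment to meditation practice, and membership of a meditation practice community". The hypothesis 2 model uses the same set: "controlling for the potentially confounding factors of age, caring status, education, mental health diagnosis, commitment to meditation practice, and active membership" of a practice community. Hypothesis 3 adds the secular/spiritual variable and "its interaction term with the amount of meditation to the model for hypothesis 1". The fourth model is built likewise: "we will add the secular versus spiritual variable and its interaction term with the amount of meditation to the model for hypothesis 2". Table 1 repeats the six factors for all four hypotheses. The Measures section marks covariates one by one, and country is not among them.

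For Aim 5 the Analysis Plan states: "Issues of confounding will be addressed through statistical adjustments as per the main analysis". One cost difference is divided by one QALY difference, and the resulting ICER is held against the thresholds of the four countries. On costs, the Discussion says "we will need to estimate costs from this information for the relevant" country's health system, and limits this to care that is not paid out-of-pocket.

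**The concern.** In a non-randomised comparison, a variable that is related to both the exposure and the outcome, and is left out of the model, is absorbed into the exposure coefficient. Country could play that part. Recruitment goes through teacher and center networks, so how much and in which tradition people practise may vary by place. The price of a mental health visit will vary by country through the plan's own costing method.

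Aim 5 is the most exposed. If those who keep practising live disproportionately in a higher-cost country, the cost difference mixes country prices with any effect of practice. The ICER would carry that mixture and would then be judged against four national thresholds. For hypotheses 1 to 4 the same mechanism could shift the practice coefficient, but by a weaker route.

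**Working it through.** The plan gives no figure to reproduce, because the point concerns a covariate list. The check has three parts.

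**1. Where country appears**

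| Analysis | Adjustment stated | Country included? |
|---|---|---|
| Hypotheses 1 and 2 | six named baseline factors | no |
| Hypotheses 3 and 4 | the same six, plus secular/spiritual and its interaction with practice | no |
| Inverse-probability-weighting sensitivity analyses | predictors described in general terms | not named |
| Aim 5, adjustment | as in the main analysis | no |
| Aim 5, elsewhere | costing of care not paid out-of-pocket; thresholds for the ICER | yes, but not as adjustment |

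So country affects the costs and the benchmark in Aim 5, but not the comparison between practice groups.

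**2. Aim 5, illustration**

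Spurious incremental cost = (cost gap between countries per person-year) × (difference in country share between practice groups). Shift in the ICER = spurious cost ÷ QALY difference. All inputs are assumptions; the documents give none of them.

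- Cost gap 500, imbalance 0.20: 500 × 0.20 = 100 per person.
- Low end, gap 250 and imbalance 0.10: 250 × 0.10 = 25 per person.
- High end, gap 2,000 and imbalance 0.30: 2,000 × 0.30 = 600 per person.
- With an assumed QALY difference of 0.02, the ICER shifts by 25 ÷ 0.02 = 1,250, 100 ÷ 0.02 = 5,000 and 600 ÷ 0.02 = 30,000 per QALY.

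The QALY side is less direct. The Analysis Plan applies the United Kingdom pilot value set and names no other, so country could enter only through differences in the EQ-HWB-9 responses themselves.

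**3. Hypothesis 1, illustration**

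From the Sampling Plan: EQ-HWB-9 SD 7.0, and an assumed gain of 4.5 points in the high-practice group against none in the low-practice group. Assumed: a country gap of 0.1 to 0.3 SD and a 10- to 30-point imbalance in country share.

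- Low end: 0.1 × 7.0 × 0.10 = 0.07 points, and 0.07 ÷ 4.5 = 1.6%.
- High end: 0.3 × 7.0 × 0.30 = 0.63 points, and 0.63 ÷ 4.5 = 14%.

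These figures treat the comparison as purely between persons. The planned model is a repeated-measures linear mixed model of past-month practice. Country is constant within a person, so it can bias only the between-person part of the coefficient.

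A small simulation shows how much this matters: 600 participants, 12 months, random intercept, no true effect, country gap 0.3 SD in outcome and 0.2 SD in practice, 25 replicates in each of two settings. With half of the practice variance within persons, the mean slope per SD of practice was 0.018 points without country and 0.011 with it. With one fifth within persons, it was 0.006 and -0.009. Leaving country out moved the slope by 0.018 - 0.011 = 0.007 points and 0.006 - (-0.009) = 0.015 points, on a scale with SD 7.0.

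**The case against.** The case for leaving the plan alone has four parts.

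- **The main models have a reasoned covariate set.** It covers time available, symptom severity, motivation and social support. Community membership and, in hypotheses 3 and 4, the secular/spiritual term already cover part of what country might carry. The documents show no link between country and amount of practice. This stands, and it limits the point for hypotheses 1 to 4 to a safeguard.
- **Aim 5 is not fully closed.** The plan also promises to account for confounders in general terms, and to run scenario and one-way sensitivity analyses. The abstract mentions sociodemographics. None of these names country, and the one explicit statement refers back to a list without it.
- **Aim 5 is exploratory, has no hypothesis, and its comparator is acknowledged as a major limitation.** This lowers the stakes. The acknowledged limitation concerns the lack of a control group, not country mix.
- **Changing the primary model departs from a preregistration of May 2024, with 341 participants already at baseline.** This is a real cost, though only one of documentation.

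Two stronger readings are tempting. A reader might infer that country could produce a false positive for hypothesis 1, by setting a cross-sectional between-country slope against a standard error of about one over the square root of the sample size. That is not the planned model, and nothing in the documents supports country gaps large enough to matter within it. A reader might also infer that all service costs will be costed by country. The Discussion restricts this to costs that are not out-of-pocket.

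**Conclusion.** The point holds, chiefly for Aim 5. Country is absent from every stated adjustment set, including the one that the cost-effectiveness analysis inherits, while part of the cost data will depend on country by the plan's own method. If country mix differs between the self-selected practice groups, the difference goes straight into incremental cost and may also reach the QALY difference.

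The size cannot be determined. A spurious 100 per person is one illustration; the assumed range of 25 to 600 shows sensitivity to the inputs, not a likely error. If country mix happens to be balanced, there is no bias.

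For hypotheses 1 to 4 the bias is probably small, and the documents give no ground for expecting a conclusion to change.

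**What to change.** **Aim 5.** Add country of residence as a fixed effect to the cost and QALY regressions. Alternatively, compute increments within each country and report them against that country's threshold. The second option matches the planned threshold comparison better but is less precise where a country contributes few participants.

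**Hypotheses 1 to 4.** Add country as a fixed effect (four levels, 3 df) to the models in the Analysis Plan and Table 1. At minimum, prespecify a country-adjusted sensitivity analysis.

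**Cost of the change.** No new data are needed, and with about 600 participants up to 3 df is a negligible loss of precision. The change should be recorded as an amendment to the preregistration before outcome analysis; results are expected in January 2028, so there is time. A sparse country may have to be merged with another in the models, but its unit costs should stay its own.

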Finally, the study aims to document the incidence and impact on daily function of any challenging, difficult, or distressing meditation-related experiences (Aim 6). Meditation-related adverse effects (MRAEs) will be defined as any challenging, difficult, or distressing meditation-related experiences that impact everyday functioning. Our aims, hypotheses, and possible interpretations are summarized in Table 1 below.

**Table 1. T1:** Protocol Design table.

Question	Hypothesis	Sampling plan (eg, power analysis)	Analysis plan	Interpretation given to different outcomes
Does regular meditation practice after initial instruction increase quality of life?	The amount of meditation practice during approximately the first year predicts practitioners’ quality of life, such that a greater amount leads to greater quality of life.	A total number of 522 gives 95% power to detect the variance in quality of life (EQ-HWB-9^a^) explained by monthly meditation practice observed in linear mixed model analysis, at a 2-tailed significance level of 0.05, accounting for an estimated 20% loss to follow-up.	Linear mixed model of the fixed effect of the amount of meditation in the past month on quality of life in the past week (EQ-HWB-9), controlling for the confounding factors of age, caring status, education, mental health diagnosis, commitment to meditation, and membership of a practice support community at baseline.	A positive/negative and statistically significant association between the amount of meditation in the past month on quality of life and in the past week will suggest that regular meditation practice after initial instruction increases/decreases quality of life in a linear fashion. A nonsignificant association will suggest an absence of evidence for either of these effects.

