Community of practice membership will be assessed by a single item and recorded at baseline and one year (“Are you an active member of a community of practice [eg, sangha, meditation group, or online communities]? Yes/No”). This will be a covariate.

Age in years will be recorded at baseline. This will be a covariate.

Caring status, including type of caring relationship, will be assessed at baseline. This will be a covariate.

Education will be assessed by a question asking, “What is the highest level of education you have completed?” and will be recorded at baseline. This will be a covariate.

Mental health diagnosis will be assessed by a single item at baseline (“Have you ever been diagnosed with a mental illness by a clinician?” Yes/No/Prefer not to say). This will be a covariate.

The cost of meditation practice will be assessed through self-reported questions asking participants whether they have spent any money related to their meditation practice, including on classes, courses, retreats, smartphone apps, resources such as mats, books, and clothes, and donations to meditation teachers or centers. These questions will be asked at baseline, monthly, and one year later.

The cost of mental health care use will be assessed via questions on type, frequency, and costs of psychological support. Specifically, participants will be asked, “In the past month, how many times did you see a… psychologist, psychiatrist, social worker, counselor, or other.” Participants will then be asked how they paid for this mental health service use (eg, “Out-of-pocket” and “Publicly funded”) and their out-of-pocket expenditure on mental health services in the past month. These questions will be asked at baseline, monthly, and one year. This will be used in the economic evaluation.

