Quality of life will be assessed at baseline, monthly, and one year, using the 9-item EQ Health and Wellbeing (EQ-HWB-9) instrument [58]. The EQ-HWB-9 captures mental (eg, depression and cognition), physical (eg, pain), and social (eg, loneliness) aspects of quality of life for the past 7 days, on a 5-point Likert scale from 1 (No difficulty) to 5 (Unable). Previous responsiveness to change analysis indicates that the EQ-HWB-9 detects meaningful changes in both mental and physical health measures [59]. This will be our primary outcome. The EQ-HWB-9 also allows for the calculation of quality-adjusted life years (QALYs), a standard measurement in health decision-making, and thus allows for the comparison of both effectiveness and cost-effectiveness with many other interventions and standard treatments [60].

Mental well-being will be assessed at baseline, monthly, and one year using the Short Warwick-Edinburgh Mental Well-Being Scale (SWEMWBS) [61,62]. The SWEMWBS includes 7 items that assess mental well-being over the past 2 weeks, on a 5-point Likert scale from 1 (None of the time) to 5 (All of the time). This will be our secondary outcome. The items in the SWEMWBS are positively worded (eg, “I’ve been feeling optimistic about the future”) and aim to capture variation in the flourishing side of the well-being spectrum, which will supplement detailed variation in the quality of life deficits captured by the EQ-HWB-9. Previous analyses of responsiveness to change indicate that the SWEMWBS detects individually meaningful improvement across a variety of mental health measures [63].

MRAEs will be measured at baseline, one year, and monthly, using the 3-item MRAEs measures [42]. The first item asks participants to indicate the frequency of any challenging, difficult, or distressing meditation-related experiences, with options ranging from “never” to “frequently.” The second item assesses the level of impairment caused by these experiences on the participant’s ability to function, with options ranging from “not at all” to “severely.” The third item asks about the duration of the impairment, with options ranging from “1 day or less” to “1 year or longer.”

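### The models for Hypotheses 1 and 2 give self-chosen practice one pooled coefficient, without baseline outcome, study month or a between/within-person split, yet Table 1 reads significance as an effect of practice

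*Protocol article*

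**What the plan says.** For Hypothesis 1 the Analysis Plan specifies a "linear mixed model analysis of the fixed effect of the amount of meditation in the past month on quality of life in the past week", adjusted for "age, caring status, education, mental health diagnosis, commitment to meditation practice, and membership of a meditation practice community at baseline". Table 1 gives the same list ("controlling for the confounding factors of age, caring status, education, mental health diagnosis, commitment to meditation, and membership of a practice support community at baseline") and repeats it for the other three hypotheses. Hypothesis 2 has the same form, with SWEMWBS as the outcome.

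The adjustment is described as "controlling for baseline differences related to time available for practice, symptom severity, motivation, and social support". The Abstract goes further: "Potential confounders, including baseline mental health symptoms, social support, and sociodemographics, will be controlled for in linear mixed models". The only mental-health covariate is the Measures item "Have you ever been diagnosed with a mental illness by a clinician", answered yes, no or prefer not to say. The same section states "Quality of life will be assessed at baseline, monthly, and one year", and SWEMWBS follows the same schedule.

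Table 1 says that a significant coefficient will suggest that regular practice raises or lowers the outcome linearly. Time-varying confounding is handled by inverse probability weighting, on a condition: "If we detect an effect of meditation practice, we will perform sensitivity analysis to examine how robust this effect is to time-varying confounders".

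**The concern.** Practice is chosen by the participant and changes from month to month. A single coefficient then mixes three things: people who usually practise more may usually be better or worse off; practice and outcome may both drift over the year; and months of more practice may be better months. Only the third is close to the statement in Table 1, and even that is open to reverse causation.

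A lifetime diagnosis item measures neither current symptoms nor their severity, so the stated control is not delivered, although direct baseline measures exist.

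Because the weighting is triggered only by a positive finding, confounding that hides a benefit (practising more when distressed) would never be examined. What is at stake is the meaning of the primary result.

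**Working it through.** **The plan's own figure.** The sample-size section assumes a common baseline of 19.6, SD 7.0, ten time points, and low, medium and high dose groups gaining 0, 2.25 and 4.5 points. A group-by-time test (Hotelling-Lawley trace, three equal groups, 5% two-sided, 95% power) returns 435 exactly if repeated measures are uncorrelated, and 222 under compound symmetry of 0.5. The article does not state the correlation. Then 435 × 1.2 = 522. So the stated size is consistent with a test of divergence over time, while the model for Hypothesis 1 has no time term.

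**Inputs.** From the article: N = 435, T = 12 months, SD 7.0. Assumed: share of variance between persons 0.6 for both outcome and practice (practice in SD units), and a correlation r between usual practice and usual outcome that remains after the six covariates. The true effect is zero.

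**Residual confounding between persons.** In a random-intercept model the pooled coefficient is a weighted mean of the within-person slope (zero here) and the between-person slope.
- Discount on between-person information: 0.4 / (0.4 + 12 × 0.6) = 0.0526.
- Within-person information per person: 11 × 0.4 = 4.4. Between-person: 0.0526 × 12 × (0.6 + 0.4/12) = 0.4.
- Weight on the between-person slope: 0.4 / 4.8 = 0.083.
- Between-person slope at r = 0.2: 7 × 0.6 × 0.2 / 0.633 = 1.326 points per SD.
- Pooled coefficient: 0.083 × 1.326 = 0.111. SE: √[49 × 0.4 / (435 × 4.8)] = 0.097. Ratio: 1.14.
- Rejection rate: P(Z > 1.96 − 1.14) + P(Z < −1.96 − 1.14) = 0.207.

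Simulation (800 runs) gives 20.6%, and 5.2% at r = 0. Over between-person shares of 0.5-0.7 for the outcome and 0.5-0.8 for practice (400 runs each), the rate is 8.5-22% at r = 0.1, 16-53% at r = 0.2 and 28-92% at r = 0.3.

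**Shared drift, r = 0.** Let practice fall 0.5 SD and the score fall 1 point over the year. The sum of squares of scaled time over 12 months is 143/121 = 1.182.
- Pooled coefficient: (0.5 × 1 × 1.182) / (4.4 + 0.25 × 1.182 + 0.4) = 0.591 / 5.096 = 0.116.
- SE 0.094; ratio 1.23; rejection rate 0.234 (simulation 22.6%).

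The result moves with the assumed drift. With 480 people, falls of 0.3 SD in practice and 0.1 SD in outcome give 8-9%; 0.6 and 0.1 SD give 18%; 0.6 and 0.2 SD give 53-62% across simulation runs.

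**What each added term does (simulation, N = 435, shares 0.6)**

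| Model | r = 0.2, no drift | r = 0, drift 0.5 SD and 1 point |
|---|---|---|
| As planned | 20.6% | 22.6% |
| + baseline outcome | 16.9% | 20.5% |
| + month | 20.1% | 5.6% |
| + both | 17.1% | 5.6% |
| Within-person term, with both | 5.1% | 5.4% |
| Person-mean term, with both | 67.4% | 3.4% |

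Month removes the shared trend, and baseline alone helps little. The split does not remove between-person confounding; it moves it into a separate, visible coefficient.

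**What the split costs.** In the planning scenario, people sit at stable doses and their scores diverge. Monthly deviations around a stable dose carry no information about that divergence. In simulation the within-person term rejects in about 4-7% of runs, the person-mean term in 91% to nearly 100%, person-mean-by-time in nearly 100%, and the planned pooled coefficient in only 16-20%.

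**Confounding that hides a benefit.** A true effect of 0.05 SD per SD of practice is 0.05 × 7 = 0.35 points; 0.35 / 0.097 = 3.6, detected in about 96% of simulated datasets. If practice correlates −0.05 with that month's state, the within-person bias is about −0.05 × 7 = −0.35 and cancels it. Detection falls to 5%, and the weighting would not be triggered.

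**The case against.** Several counter-arguments have force.

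- **The Analysis Plan mentions a longitudinal constrained analysis under missing data**, which normally models the outcome over time, and an article may condense. But the model is set out in the Analysis Plan and in Table 1, and neither carries a time or baseline term. A common baseline mean is normally justified by randomisation, which is absent here. The time term may exist in a fuller document; the article should say so.
- **A reader might infer that baseline outcomes are never used.** The text does not support that. The weighting targets prior practice and benefit, which plausibly includes earlier outcomes, and the censoring weights draw on baseline predictors. The accurate statement is that they are not covariates in the models.
- **A reader might take the planned growth from 0 to 4.5 points as evidence of a shared time trend.** It is the assumed dose effect; the low-dose group is given no change.
- **Baseline is not clean.** Participants enter after initial instruction or at least a month of practice, so adjusting for baseline may absorb some early effect. This stands as a caveat.
- **A null result is read only as absence of evidence**, so masked benefit produces no false claim. True, but the check would still be missing where it is informative.

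**Conclusion.** The point holds. The pooled coefficient cannot carry the reading that Table 1 gives it, and the symptom-severity claim is not supported by the covariate offered.

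The size is conditional. The false-positive rate is about 5% with neither residual confounding nor drift, about 20% at r = 0.2 with between-person shares of 0.6, and about 8-60% over the drifts tried. A reader might infer that the plan has a known, large false-positive rate. The article supports none of the correlations, variance shares or drifts used, so these figures show what can happen and are not a prediction.

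A reader might also infer that all inference should move to the within-person coefficient, at the price of a wider interval. The sample-size section does not support that. Its scenario is a cumulative divergence between stable doses, which that coefficient misses almost entirely, so the move would change the estimand. Nor is that coefficient immune to reverse causation.

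**What to change.** For Hypotheses 1 and 2, carried into 3 and 4:

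1. Add month as a categorical fixed effect and the baseline value of the outcome as a covariate, noting that baseline follows initial instruction and may absorb some early effect.
2. Split monthly practice into the person's mean and the monthly deviation from it. Report both, and describe between-person results as associations.
3. Test the divergence assumed in the sample-size section with a practice-by-time term adjusted for baseline.
4. Run the inverse-probability-weighted analysis whatever the primary result, with baseline and prior outcome in the weights.
5. Delete or correct the symptom-severity claim in the Analysis Plan and the matching claim in the Abstract.
6. In Table 1, replace the wording on raising or lowering the outcome with wording on association, unless the weighted analysis agrees.

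The cost is a dated amendment and a few model terms; all the data are already scheduled. Reporting two practice components and a time interaction means naming in advance which one answers Hypothesis 1. With results expected in January 2028, this can be settled before analysis; later it would look data-driven.
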